# Study treatments

## Description of investigational product(s)

The study participants will be randomization to either;

1. **Hibitane®** (investigational treatment), manufactured by Bioglan AB, [name]. 1 ml contains 10 g chlorhexidine gluconate (1%) and 20 mg Cetostearyl alcohol.

Therapeutic indications: anti-septic use for clinical vaginal examinations, especially during delivery.

Administration time: 3 months with additional treatment in case of infection relapse during the observational phase of the study, 3-6 months after inclusion.

Known adverse event: irritation on skin and mucosa.

Restrictions: allergy to the active substance, avoid contact of active substance with brain or meningeal tissue, or ear canal due to neurotoxicity. Hibitane® is approved for vaginal use even during pregnancy and lactation

or

1. **Fluconazole** (control or standard treatment), manufactured by different producers. Oral capsules of 150 mg fluconazol + 139 mg laktos.

Therapeutic indications: different types of fungal infections (cryptocock meningitis, coccidioido mycosis, invasive candidiasis) including mucosal Candia albicans infections.

Administration time: 3 months with additional treatment in case of infection relapse during the observational phase of the study, 3-6 months after inclusion.

Known adverse events: most common side effects are; headache, abdominal pain, nausea, vomiting, diarrhea, skin rashes. For more information, see attached product resume.

Restrictions: allergy to the active substance, doses should be adjusted in case of reduced renal or liver function, concomitant use of medications with known risk of increasing QT-interval and be metabolized via cytocrom P450 (CYP)3A4 (cisaprid, astemizole, pimozid, quinidine and erythromycin). Fluconazole is not approved during pregnancy. For more information, see attached product resume.

Both medication will be prescribed and handled routinely by the pharmacies.

## Dose and administration

1. Hibitane® is a cream and will be applied vaginally by the help of a 10 ml plastic syringe (Braun, Melsungen, Germany, CE 0123), provided to the participants randomized to Hibitane®. During the first week of treatment 8 ml is used every night at bedtime and thereafter 8 ml will be used at night once a week for 11 consecutive weeks. The dose of 8 ml is considered an adequate to be applied in the vagina for achieving treatment effect. Most of the cream will stay in place, but a small portion will leak and a genital pad is recommended. Dose changes or withdrawal of the medication will be considered in case of AE.
2. Fluconzole® oral 150 mg capsules will be used every 3 days for the first 3 doses, thereafter as prophylactic treatment with 150 mg/week for another 11 consecutive weeks. The fluconazole regime serves as the reference medication normally used for recurrent vulvovaginal candidiasis according to international recommendations and FASS. Fluconazole can be taken regardless of food intake. Dose changes or withdrawal of the medication will be considered in case of AE.

## Packaging, labeling, and handling of investigational products(s)

Both study drugs will be prescribed and marked according to usual practice at the pharmacy. No administration of the drugs will be handled by study personal.

**Hibitane® 1% vaginal cream**

What will be new for the participants is the handling and administration of Hibitane® 1% vaginal cream. The cream comes in a plastic bottle of 250 ml which should be stored at room temperature (< 25° C). After the bottle is opened it can preferable be stored in a fridge between use. Participants randomized to Hibitane® will be provided with 10 ml plastic syringes in surplus for administrations. Participants will be instructed how to insert the cream in the upper part of the vagina. An expire date is marked on each bottle, and the bottle can be stored after it has been opened for at least 3 months according to information from the manufacturer.

A written information of the Hibitane administration is provided.

**Fluconazol®, oral capsules 150 mg**

Most participants are probably already familiar to the fluconazole regime since they suffer from recurrent candida infections. The capsules come in paper packaging of 6 capsules in each. A total of 18 capsules will be prescribed, but additional prescriptions might be needed if the infection relapses. The packaging is marked at the pharmacy and can be kept at room temperature (< 30° C). The capsules should be administered approximately at the same time every day.

A written information of the fluconazole administration is provided.

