## Primary objective

To analyze if daily vaginal application of 8 ml of Hibitane® for one week and thereafter once a week for another 11 consecutive weeks is at least as effective as fluconazole 150 mg capsules every third day for the first three doses and thereafter 150 mg once a week for another 11 consecutive weeks regarding treatment- and prophylactic efficacy for recurrent vulvovaginal *Candida albicans* infection*.*

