## Overall study design

The study is a 6 months clinical Phase II trial to compare if 1% chlorhexidine gluconate vaginal cream (Hibitane®) is at least as effective and safe as fluconazole (reference treatment) for culture-verified recurrent vulvovaginal candidiasis. The study is a randomized open non-inferiority trial with parallel treatment groups. The trial is not possible to blind for neither participants nor investigators due to the differences between study treatments. There is low risk of bias since the primary outcome variable is objective (negative vaginal culture for *Candida albicans*).

The rational for the study is to find an alternative treatment to fluconazole for RVVC with high tolerability and without cytotoxic effect on epithelial cells and negative impact on the vaginal microbes.

The participants will be randomization to;

- Investigational medication with Hibitane® vaginal cream 8 ml every night for a week and then prophylactic treatment with 8 ml/week for another 11 weeks

or

- Reference treatment with Fluconazole® 150 mg (oral capsule) every 3 days for the first 3 doses, then prophylactic treatment with 150 mg/week for another 11 weeks

Please see section 7 for more details on randomization and study treatments.

Figure 1 Study design

| **Visit** | **1** | **2** | **3** | **4** | **5** |
| --- | --- | --- | --- | --- | --- |
|  |  | CHG | Chlorhexidine gluconate  vaginal application  8 ml/w, 11 w | |  |
|  |  | 8 ml/day,1 w  R |  |  | N=30 |
|  |  |  | Fluconazole  oral capsules  150 mg/w, 11 w | |  |
|  |  | FLZ  150 mg/day,1w |  |  | N=30 |
| **Week:** | **-1** | **0** | **1** | **12** | **24** |
|  | Screening | Inclusion/  Baseline  Randomization | Follow-up | Follow-up | Follow-up and end of treatment |

##

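### Figure 1 shows fluconazole daily for one week (1,050 mg), while three text statements give three doses in the acute course (450 mg)

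*Protocol*

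**What the plan says.** The fluconazole schedule appears in four places in the protocol.

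- Primary objective: "fluconazole 150 mg capsules every third day for the first three doses and thereafter 150 mg once a week for another 11 consecutive weeks".
- Overall study design, text: "150 mg (oral capsule) every 3 days for the first 3 doses, then prophylactic treatment with 150 mg/week for another 11 weeks".
- Dose and administration: "oral 150 mg capsules will be used every 3 days for the first 3 doses", followed by weekly prophylaxis for a further 11 weeks.
- Overall study design, Figure 1: the fluconazole arm is labelled 150 mg per day for 1 week, followed by 150 mg per week for 11 weeks.

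The handling section for the capsules adds three statements: the pack size ("The capsules come in paper packaging of 6 capsules in each"), the quantity ("A total of 18 capsules will be prescribed, but additional prescriptions might be needed if the infection relapses") and an instruction on timing ("The capsules should be administered approximately at the same time every day").

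**The concern.** Fluconazole is the active comparator in a non-inferiority trial. Its acute course leads directly to the primary endpoint, the culture taken one week after active treatment, and the sample size section assumes 86% success on it. The reference exposure should therefore be stated once and without conflict.

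Two other parts of the plan depend on the same statement.

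- **Per-protocol set.** The abbreviations list defines the per-protocol analysis strictly: only women who completed the study fully in line with the protocol, with no deviations. The statistical methods plan an efficacy analysis in that set. A woman who took a capsule daily in the first week would deviate from the dosing section but comply with Figure 1.
- **Safety.** The quality assurance section ties the major identified risk of the study to fluconazole, and the proportion of women with adverse events is a secondary endpoint. An inconsistent comparator dose carries over into that comparison.

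The drugs are prescribed through pharmacies and study personnel do not administer them. What each woman takes therefore depends on the prescription and the written instruction, and both need a single schedule behind them.

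**Working it through.** **Inputs.** Capsule strength is 150 mg. The acute course is 3 doses (Primary objective; Overall study design, text; Dose and administration) or 7 doses (Figure 1, daily for one week). Prophylaxis is 11 weekly doses in every version. The pack size is 6 and the quantity prescribed is 18 (handling section for the capsules).

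**Step 1: reproduce the plan's figure of 18.** Capsules needed = acute doses + 11. Capsules supplied = 6 × (capsules needed ÷ 6, rounded up).

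| Schedule | Needed | Packs of 6 | Supplied | Spare |
| --- | --- | --- | --- | --- |
| Text | 3 + 11 = 14 | 14/6 = 2.33, so 3 | 18 | 4 |
| Figure 1 | 7 + 11 = 18 | 18/6 = 3 | 18 | 0 |

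Two packs hold 12 capsules, which is 2 short of the 14 that the text schedule needs. Three packs is therefore the smallest whole-pack supply under either schedule. The figure of 18 is reproduced both ways and does not discriminate between them.

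**Step 2: size of the contradiction.**

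- Acute course: 3 × 150 = 450 mg (text) against 7 × 150 = 1,050 mg (Figure 1). The difference is 600 mg and the ratio 1,050/450 = 2.3.
- Whole course: 14 × 150 = 2,100 mg against 18 × 150 = 2,700 mg. The difference is again 600 mg, so all of it lies in the acute phase, before the primary culture.

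**Step 3: is the label in Figure 1 a reading error?** The cell is legible, and its counterpart for chlorhexidine (8 ml per day for 1 week) agrees with the text for that arm. The label for fluconazole has the same daily-for-one-week form, but there it conflicts with the text.

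**The case against.** The strongest defence is that the dose is settled by the prose. The primary objective, the design text and the section devoted to dosing agree, and the design section sends the reader to section 7 for details of treatment. Figure 1 is a schematic and is loose elsewhere: it marks week 24 as the end of treatment, although the visit schedule has prophylaxis completed at week 12. On this view one cell is mislabelled and nobody would dose from it. Most of this stands. It limits the point to an inconsistency with one outlier, and it does not remove it, because the figure still states a comparator dose that the text contradicts.

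A reader might infer more than the protocol supports, in four ways.

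- **That the 18 capsules confirm the figure.** They equal 7 + 11 exactly, but the pack size stands in the sentence just before, and rounding 14 up to whole packs also gives 18. Container surplus occurs in the other arm too: 18 applications of 8 ml are 144 ml, from a 250 ml bottle. The four spare capsules under the text schedule are not a defect.
- **That the reference to every day confirms daily dosing.** It can be read as advice on the time of day. Read literally as daily dosing, it also contradicts Figure 1, where 11 of the 18 doses are weekly. It is loose wording and no evidence for either schedule.
- **That the comparator exposure is not fixed at all.** Three concordant statements against one figure label do not support that.
- **That a woman is told to take all 18 capsules as her course.** The 18 is a quantity prescribed. Compliance is assessed at visits and by weekly diary, with no capsule count described, and the written participant information is not shown.

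**Conclusion.** The point holds as an internal contradiction about the comparator dose. Figure 1 implies 7 acute doses (1,050 mg), and three text statements give 3 (450 mg), before an identical weekly phase. The gap is 600 mg, or 2.3-fold over the acute course, and it falls entirely before the primary culture.

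This assumes that daily for one week means seven doses of one capsule, and it is the gap that would arise if anyone dosed from the figure. The documents do not show that anyone would, and they give no basis for estimating an effect on fluconazole's culture success or on power, so none is claimed.

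It should be corrected. The conflict concerns the reference arm of a non-inferiority comparison, the adverse event comparison and a per-protocol set that tolerates no deviations. The three agreeing text statements keep it from being more serious. Which schedule is right is a clinical matter on which no view is taken.

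**What to change.** 1. Reconcile Figure 1 with the Primary objective, the text of Overall study design and Dose and administration, so that all give one acute fluconazole schedule confirmed by the responsible clinicians.
2. In the handling section, clarify whether the sentence on taking capsules at the same time refers to time of day only. State how the 18 capsules follow from the confirmed schedule and the pack size.
3. Check the written participant instruction and the definition of adherence for the per-protocol set against that schedule.

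The cost is wording in the protocol and the participant instruction, with no extra participants or visits. If the reconciliation changed the dose given in the text, the protocol's own section on substantial changes would apply, since it names dosage among the changes that need approval before they are implemented.

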## Drug accountability and treatment compliance

Compliance will be evaluated at the follow-up visits and the participants will fill out a web based digital weekly dairy how they have taken the study medications. If a dose is missed, it should be administered as soon as possible as stated in the study protocol.

## Randomization

The randomization ratio between the treatment groups will be 1:1. A computer generated block randomization of 15 participants will be performed by the research midwife. Randomization to the study medications will be carried out via opening of opaque sealed envelopes in consecutive order. All women will be identified through a patient log with name and Swedish personal identification number and a study identification number, used on all CRFs (paper and electronic). The randomization will not be blinded to neither participants nor investigators due to the differences in study medications. The primary outcome variable is objective (negative vaginal culture for *Candida albicans*) with low risk of bias.

Subjects are included/randomized consecutively as they are found to be eligible for inclusion in the study. If a subject discontinues their study participation, their subject code will not be reused and the subject will not be allowed to re-enter the study again.

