4. The content of lactobacillus in vaginal wet mount will be analyzed and semi-quantified first at baseline/inclusion and then at 3 follow-ups; 1 week after treatment, 3 months’ follow-up after prophylactic treatment and at 6 months’ follow-up. Routine procedure for wet mount (vaginal secretion with NaCl) will be performed and the amount of lactobacilli will be graded in a light microscope with high magnification (40x and 100x) (Olympus CX41) as either normal quantity (more lactobacilli compared to number of epithelial cell/view field) or reduced (less or absent lactobacilli compared to number of epithelial cell/view field). Differences in proportion of women with normal/reduced quantity between study groups x time will be analyzed. The two investigators will before the study starts, analyzed a number of wet mounts together for inter-rater reliability. All wet mounts will be photo documented via a camera connected to the microscope placed at the department of obstetrics and gynecology, Danderyd Hospital. These photos will be blinded and evaluated by the two investigators together.
5. Data on events of relapses will be collected during the prophylactic and observational phases of the study. The participants will be provided with equipment to collect self-sampled vaginal cultures for *Candida albicans* at home in case of new symptoms of infection. They can also contact the research midwife who could help out with the cultures if needed. Data on relapses will be reported in the CRF.
6. Biopsies from the vaginal mucosa will be used to study possible toxic effect on the vaginal epithelial cells. The biopsies will be taken at baseline/inclusion and at the 3 months’ follow-up and analyzed by histopathology and immunohistochemistry. The biopsies are 3-4 mm, taken by biopsy forceps after local anesthetics. The purpose of the biopsies is to investigate how CHG affect the vaginal mucosa causing possible toxic reactions of the epithelium and impairment of the local immune response. The biopsies will be microscopically examined using ordinary histopathological staining as well as immunohistochemistry for inflammatory and immunological markers. Also PCR analyses for antimicrobial peptides, cytokines, kemokins, cationic intrinsically disordered antimicrobial peptides (CIDAMP) will be performed. Biopsies from participants allocated to FLZ will serve as controls.

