## Reporting and registration of Adverse Events

At each study visit, adverse events (AE) are continuously registered, starting from start of treatment with the investigational products, up to and including 12 weeks after the subject has ended their treatment with the investigational products. All AE that occur during the study and which are observed by the investigator/study midwife or reported by the subject will be registered in the CRF regardless of whether they are related to the investigational product or not. Assessment of causal relationship, severity, and whether the AE is considered to be an SAE or not will be done by the investigator directly in the *CRF*. The subjects can also report AEs in the digital weekly diary or via communication with the investigator/study midwife. At minimum, for each AE/SAE, a description of the event is recorded (diagnosis/symptom if diagnosis is missing), start and stop dates, causal relationship, severity, if the AE is considered to be an SAE or not, measures and outcome. These data will also be reported in the participant’s medical record.

All reported new symptoms in both study groups will be evaluated as a possible AE.

All AE shall be registered in the CRF from start of treatment to 12 weeks after end of prophylactic treatment *as above (section 9.3, Reporting and registration of Adverse Events)*.

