# Statistics

## Analysis population

The study is a RCT controlled non-inferior trial with 60 women randomly assigned to either vaginal chlorhexidine gluconate (N=30) or oral fluconazole (N=30). Baseline plus 3 follow-up visits (baseline/inclusion, 1 week, 3 months and 6 months) are planned.

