## Quality Assurance and Sponsor oversight

The clinical trial will be performed at the research department at the Department of OB&GYN, Danderyd Hospital. The sponsor has the responsibility for the monitoring plan and to assure direct access to all source data for monitoring, audits and inspections.

Only 3 personnel will be involved in the study; the principal- and co-investigator together with the research coordinator. The study personnel have long experience of working together and have planned the study in close co-operation. No special training of personnel is needed.

The study coordinator role is to book the appointments for the participants, collect data from vaginal cultures and other laboratory tests, handle the CRFs and be of help during monitoring and audits. Any AEs can directly be reported to the study coordinator and further reported to the investigators and sponsor if needed.

The principal (=sponsor) and co-investigator will conduct the study visits, give the oral and written information and collect the signed consents, check the inclusion- and exclusion criteria and decide on the final inclusion of the participants.

The major risk of the study has been identified to be correlated to the study drug fluconazole which serves as the reference treatment in the trial. Fluconazole is an approved medication and caution to avoid known AEs has been taken in the inclusion- and exclusion criteria in the protocol. No serious AEs with Hibitane is expected. Any AEs can be reported directly to the study coordinator or by the use of the electronic weekly dairy.

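### Section 7.5 pairs a 1:1 ratio with blocks of 15, an odd size that cannot balance within a block, and gives the randomization to a member of staff who has participant contact

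*Protocol*

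**What the plan says.** Section 7.5 (Randomization) opens with "The randomization ratio between the treatment groups will be 1:1". The next sentence is "A computer generated block randomization of 15 participants will be performed by the research midwife". Allocation then works as follows: "Randomization to the study medications will be carried out via opening of opaque sealed envelopes in consecutive order". The section does not say who prepares, holds or opens the envelopes. The trial is open: "The randomization will not be blinded to neither participants nor investigators due to the differences in study medications".

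The study-design figure and section 10.1 (Analysis population) plan 60 women, 30 per arm.

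The research midwife appears elsewhere as a participant contact. Under Procedures and flow chart, participants contact her about suspected relapses. Section 8.1.2 says of relapse sampling: "They can also contact the research midwife who could help out with the cultures if needed". Section 9.3 gives a study midwife a part in recording adverse events: "All AE that occur during the study and which are observed by the investigator/study midwife or reported by the subject".

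Section 11.1 states "Only 3 personnel will be involved in the study" and lists two investigators and a research coordinator, but no midwife. There the coordinator books appointments and collects culture results, while the investigators check eligibility and decide on inclusion.

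**The concern.** Two consecutive sentences of section 7.5 do not fit together. A permuted block balances two arms only if its size is even. With 15, whoever builds the list must choose among several schemes: the surplus arm drawn at random, always the same arm, alternating between arms, or blocks of 30 with 15 per arm. The protocol selects none of them, so the list cannot be checked against it.

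The second matter is concealment. The person who generates a sequence can know every coming allocation, and opaque envelopes hide it only from others. Section 7.5 and the overall study design argue that bias is low because culture is an objective outcome. That addresses bias in assessing the outcome. It does not address selection, which happens before any culture is taken and which no analysis can fully undo. Some secondary endpoints, such as the symptom and examination scores, are also less objective than culture.

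**Working it through.** **Inputs.** Ratio 1:1 and block size 15 (section 7.5); 60 women, 30 per arm (section 10.1); success 86% in both arms, margin 30 percentage points, α 5%, power 90%, 23 per group (section 10.4).

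**Block arithmetic.** 15/2 = 7.5, so the closest possible split is 8:7. 60/15 = 4 blocks. If k blocks give the surplus to chlorhexidine, that arm has 8k + 7(4 − k) = 28 + k women.

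**Final split if the surplus arm is random with probability 1/2 per block** (an assumption, as the protocol gives no rule). P(k) = C(4,k)/16:

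| k | CHG:FLZ | Probability |
|---|---|---|
| 0 | 28:32 | 1/16 = 6.25% |
| 1 | 29:31 | 4/16 = 25% |
| 2 | 30:30 | 6/16 = 37.5% |
| 3 | 31:29 | 4/16 = 25% |
| 4 | 32:28 | 1/16 = 6.25% |

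So 30:30 has probability 37.5%, an imbalance of two 50%, and an imbalance of four 12.5%. If the same arm always receives 8, the result is 32:28 with certainty. Only k = 2 gives 30:30.

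**The protocol's own sample size.** n per arm = (z₁₋α + z₁₋β)² × 2 × 0.86 × 0.14 / 0.30². At one-sided 5% this is (1.645 + 1.282)² × 0.2408 / 0.09 ≈ 22.9, so 23 per arm and 46 in all. The stated figure is reproduced. At one-sided 2.5% the same formula gives 29 per arm (58), which does not match.

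**Effect of imbalance on power.** Power = Φ(0.30/SE − z₁₋α), with SE = √[0.86 × 0.14 × (1/n₁ + 1/n₂)], if all 60 are evaluable:

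| Split | One-sided 5% | One-sided 2.5% |
|---|---|---|
| 30:30 | 95.58% | 91.75% |
| 31:29 | 95.56% | 91.72% |
| 32:28 | 95.51% | 91.64% |

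The worst split costs 0.07 points at one-sided 5% and 0.11 points at one-sided 2.5%, about 0.1 to 0.2 points at most when rounded figures are compared.

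**Concealment: the sections side by side.** Section 7.5 assigns the computer-generated randomization to the research midwife and names no independent person for any step. Her documented contacts (relapse reports, relapse cultures, adverse events) all come after randomization. Section 11.1 gives booking to the coordinator and inclusion to the investigators. The documents therefore show a sequence-holder working close to the participants, but not one who books or enrols them. If midwife and coordinator are the same person, she would both know the sequence and schedule the randomization visit. If they are different people, section 11.1 leaves out someone with a central task.

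**The case against.** Four points can fairly be made on the other side.

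- **The ratio is not a promise about each block.** A 1:1 ratio can be read as an expectation over the trial. Blocks of 15 with a random surplus arm can be generated, favour neither arm on average and may reach 30:30. This stands. A reader might infer that the randomization is impossible to carry out, or that 1:1 cannot be reached. The documents do not support that: only balance within a block is impossible.
- **The figure may mean 15 per arm.** Blocks of 30 divide 60 exactly. This is possible, but section 7.5 counts 15 participants and does not say per arm. It is a reason to clarify the text, not evidence that the text is right.
- **Safeguards exist.** Envelopes are opaque, sealed and opened in order; women are randomized consecutively once culture and PCR results are known; the investigators decide on inclusion; and a hospital microbiology department reads the primary-endpoint cultures. These narrow the room for selection and lower the severity. They do not hide the sequence from its author.
- **In an open trial the contact person learns each allocation anyway.** That is true after randomization. Concealment concerns allocations not yet made.

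A reader might also infer that the midwife belongs to the three-person team and can steer women to particular envelopes. Section 11.1 does not name her, and the protocol nowhere says that she books, enrols or passes on the sequence.

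**Conclusion.** The point holds as an inconsistency to be corrected and a moderate weakness in concealment; it does not invalidate the design. The odd block size conflicts with 1:1 balance inside every block, and the planned 30:30 depends on an unstated rule. The 37.5% / 50% / 12.5% distribution assumes that the surplus arm is random and that all four blocks are filled. The consequence for power is negligible under the protocol's own assumptions, so no claim of lost power is warranted.

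The concealment weakness rests on reading section 7.5 as it is written, with the midwife producing the computer-generated sequence. Its size cannot be calculated from the documents. It depends on whether she and the coordinator in section 11.1 are the same person, and on who prepares and handles the envelopes. Because randomization is specified in the protocol itself, this is not a detail left to the analysis plan.

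**What to change.** In section 7.5:

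1. Replace 15 with even block sizes, preferably varied at random and not disclosed to recruiting staff. For example, three blocks of 4, four of 6 and three of 8 in random order give 12 + 24 + 24 = 60 and exactly 30:30.
2. Have the list and sealed envelopes prepared by someone who does not book, enrol or follow participants, such as a hospital statistician, and state who holds and opens the envelopes.
3. Reconcile the research midwife of section 7.5 with the personnel list in section 11.1.

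There is one trade-off. In an open trial, the last places in a block become certain once one arm is used up. For a block of a:b whose composition is known, the expected number of such places is a/(b + 1) + b/(a + 1). That is 8/8 + 7/9 = 1.78 of 15 (11.9%) for 8:7, 1.5 of 6 (25%) for 3:3, and 1.33 of 4 (33%) for 2:2. A small fixed even block would thus repair the arithmetic but be easier to guess, which is why the sizes should vary and stay undisclosed.

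The cost is a few sentences of protocol text and a short list-preparation task outside the clinic team. Sample size, visits and analysis are unchanged.
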